### FD-OCT guidance

FD-OCT images will be acquired at the site of AICL with a commercially available system (C7 System; LightLab Imaging Inc/St Jude Medical, Westford, Massachusetts, United States) after the FD-OCT catheter (C7 Dragonfly; LightLab Imaging Inc/St Jude Medical, Westford, Massachusetts, United States) is advanced to the distal end of the target lesion. The entire length of the region of interest will be scanned using the integrated automated pull-back device at 20 mm/s. During image acquisition, coronary blood flow will be replaced by the continuous flushing of contrast media directly from the guiding catheter at a rate of 4 ml/s with a power injector in order to create a virtually blood-free environment. All images will be recorded digitally, stored, reviewed and analyzed with proprietary software (LightLab Imaging) after confirming proper calibration settings of the Z-offset. Immediately after confirmation of successful FD-OCT image acquisition, the following measures will be performed: minimal lumen area (MLA) (defined as cross section area at the smallest lumen area level), proximal reference lumen area (pRLA) (defined as cross section at the frame with largest lumen within 10 mm proximal to MLA and before any major side-branch), distal reference lumen area (dRLA) (defined as cross section at the frame with largest lumen within 10 mm distal to MLA and before any major side-branch) and mean reference lumen area (mRLA) (defined as (pRLA + dRLA)/2).

On the basis of these parameters, AS% will be calculated using the following formula: (mRLA-MLA)/mRLA × 100.

PCI will be performed when one of the following conditions will be present: AS% ≥ 75%, AS% from 50% to 75% with MLA <2.5 mm^2^, and/or major plaque ulceration evidence at FD-OCT. Major plaque ulceration will be defined as a recess in the plaque beginning at the luminal-intimal border [4]. The described criteria have not been used in the past and have been developed for the present study. At the time the protocol was conceived, only three small studies have directly compared FD-OCT with FFR in order to find a cutoff for one of the anatomic parameters provided by FD-OCT in order to predict FFR [18-20]. Nevertheless a definite cutoff has not been identified and a broadly poor accuracy of FD-OCT in detecting a FFR of ≤0.80 has been described.

For this reason the definition of FD-OCT criteria for this study was based on the concept that no unique cutoff value of any parameter is currently known. In particular, the percentage and small residual cross-section area are known to correlate independently with the functional significance of coronary stenosis [21]. Overall, the accuracy of MLA seems to compare favorably with that of AS%, but MLA cutoffs are known to differ across different coronary vessels and study populations [22].

Moreover, when the AS% is above 75 to 80%, false positives are virtually absent [18], meaning that at these levels AS% is probably a reliable cutoff for intervention (first criterion). When such an extreme situation is not present, we decided to improve the accuracy by combining small MLA with appreciable AS% (second criterion) in order to limit false positives (and indirectly adjusting for vessel size). In dealing with a gray zone for the AS% parameter, a looser MLA cutoff of 2.5 mm^2^ has been chosen in this case in order to reduce the possibilities of false negative.

Finally, since some adverse events may occur in patients with FFR-negative lesions (0.2% occurrence of MI and revascularization rate of 3.2% in FFR >0.80 group of the FAME study, and 3.3% occurrence of combined primary endpoint in the defer group of the DEFER study) [6,7] and untreated lesions with complex morphology may be responsible, we hypothesize that stenosis with the typical features of complicated atherosclerosis (as detectable by FD-OCT) may particularly benefit from treatment (third criterion). In this case only major plaque ulceration was considered as a criterion as it is the hallmark of existing plaque instability. The presence of a thin fibrous cap atheroma (TCFA) was not identified as a criterion for PCI or AICL. Indeed, even if TCFA are associated to possible future plaque instability and may have a prognostic relevance [23], no randomized studies have so far shown a clinical benefit in a preventive stenting strategy for this kind of lesion.

In FD-OCT patients undergoing PCI, FD-OCT will also be used to check PCI results and to guide further optimization of the PCI results, if required. In particular, after the procedure a FD-OCT run will be performed and further intervention (balloon dilation and/or stent implantation) will be performed in the presence of: major stent strut malapposition (defined as a distance between the strut and vessel wall of greater than 350 μm or <350 but >200 μm for a length >600 μm (appreciable in >3 contiguous frames at a pull-back speed of 20 mm/sec) [9,24]), major stent under-expansion (defined as: in-stent minimal cross-section area of <75% of the RLA [9,25]) and major edge dissection (defined as dissection >600 μm (appreciable in >3 contiguous frames at a pull-back speed of 20 mm/sec) [24,26]).

The feasibility of FD-OCT guidance for PCI has been recently reported by several authors [9,27] and it has been shown that it may improve prognosis when compared to the ‘classical’ angiographic guidance [28]. The concept of FD-OCT guidance for PCI is based on the possibility that stent-related complications may influence the long term the occurrence of stent failures [29]. Yet, (minor) stent complications such as edge dissections, plaque prolapse, stent under-expansion, and malapposition are frequently detectable by FD-OCT and may evolve positively in the majority of cases managed conservatively [30]. In a retrospective analysis of our FD-OCT procedures, the above mentioned quantitative cutoffs for treatment of FD-OCT detectable complications were found in one third of cases (unpublished data). Thus, we planned to try to correct by further treatment, only such ‘major’ stent complications among the minor ones detected by FD-OCT.

### Post-procedural management

All patients will undergo cardiac damage markers (Creatin-kinase-MB and Troponin I) assessment before the procedure (when feasible), at 6 and 24 hours after PCI. Thereafter, further blood samples will be performed only if clinically indicated. After PCI, patients will be given aspirin (75 to 100 mg/die) on an ongoing basis and clopidogrel (75 mg/die) according to the European Society of Cardiology Guidelines [16].

### Data set and clinical outcome measures

Clinical data (risk factors, medical history) of enrolled patients will be collected in a dedicated electronic database at the time of the intervention procedure. The date of discharge will be systematically recorded. After discharge, patients will be contacted by phone or ambulatory visit at 1, 6, and 13 months. A follow up coronary angiography will be performed only in the case of typical symptoms or signs of ischemia on noninvasive testing, whereas repeat revascularization will be undertaken in the case of significant (>50%) angiographic stenosis.

In the case of suspected adverse clinical events, pertinent medical records will be carefully reviewed to ascertain the occurrence of MACE. Deaths of an unknown cause will be considered of cardiovascular origin. MI will be defined according to the third universal definition of myocardial infarction by a combination of chest discomfort, typical ECG modifications and the dynamic increasing of troponin T (>99^th^ percentile upper reference limit) related to atherosclerotic plaque rupture, ulceration, fissuring, erosion, or dissection with resulting intraluminal thrombus in one or more of the coronary arteries (Type 1 MI) [31]. Post-procedural MI will be defined as a rise of creatinin-kinase MB more than five times the 99^th^ percentile upper reference limit during the 48 hours after PCI [32]. Thereafter, peri-procedural MI (Type 4a MI) will be defined by a combination of symptoms, typical ECG modifications and elevation of troponin values of more than five times the 99th percentile upper reference limit in patients with a normal baseline, or a rise of troponin values of greater than 20% if the baseline values are elevated, and are stable or falling [31].

TVR will be defined as repeated clinically-driven revascularization by either PCI or coronary-aortic bypass grafting involving the treated vessel. Stent thrombosis will be classified by the Academic Research Consortium definition as definite, probable, or possible and as early (0 to 30 days), late (31 to 360 days), or very late (over 360 days) [33].

Detailed clinical assessment of angina status will take place at one and thirteen months by asking the patients to fulfil the SAQ, a disease-specific functional status measure to quantify the physical and emotional effects of coronary artery disease [34]. It consists of a questionnaire of eleven questions grouped into five main scales measuring clinically important dimensions of coronary artery disease: physical limitation, angina stability, angina frequency, treatment satisfaction, and disease perception. SAQ is scored by assigning each response an ordinal value, beginning with 1 for the response that implies the lowest level of functioning, and summing items within each of the five scales. Scale scores are then transformed to a 0 to 100 range. Because each scale monitors a unique dimension of coronary artery disease, no summary is generated. Yet, due to the evidence of overlaps between the five assessment scales, a <90 score on the angina frequency scale will be used to define ‘significant residual angina’ (see primary study endpoints session) [34].

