## Methods/Design

### Study design

The FORZA study is an open label prospective single centre randomized trial comparing the costs and the rate of adverse clinical outcomes in patients randomized to FFR versus FD-OCT guided PCI on AICL.

Consecutive patients with evidence of AICL, defined as a coronary lesion with a visually estimated percentage diameter stenosis ranging from between 30 and 80% [15], will be prospectively enrolled and randomized to FFR guidance or FD-OCT guidance at a ratio of 1:1.

Each patient will complete a Seattle Angina Questionnaire (SAQ) before intervention, at one month, and thirteen months follow up. Details on SAQ are reported in the Methods/Design section. FFR and FD-OCT assessment will be performed at the site of AICL according to technical details reported in the Methods/Design section below. The study flow chart is summarized in Figure 1.

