### Study endpoints

The occurrence of significant residual angina (<90 score at SAQ angina frequency scale) at 13 months represents the primary endpoint of the study.

Major cardiovascular events (MACE), defined as the occurrence of death, myocardial infarction (MI) and target vessel revascularization (TVR), will be prospectively assessed. Since the rate of MACE is anticipated to be low, and most of the procedures in patients with AICL are performed with the aim of improving symptoms, the recurrence of significant angina (defined as an SAQ score <90 on the angina frequency scale) will be prospectively assessed as well.

The first secondary endpoint will be the combined endpoint of recurrence of significant angina or MACE at 13 months follow up. However, in the case of a MACE rate absolute difference of >1% between the two study arms, this combined endpoint will be considered as the primary endpoint of the study.

A further secondary endpoint will be the global costs of the strategy (FFR or FD-OCT guided) at one and thirteen months follow up.

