### Procedure description

A guiding catheter (shape and size chosen by the operator) will be placed at the coronary ostium. Then, according to randomization, FFR or FD-OCT assessment will be performed as described below. PCI will be performed at the same time or in a second procedure (‘staged procedure’) according to the decision of the operator only if the pre-specified FFR or FD-OCT criteria are fulfilled, otherwise the patient will be discharged on optimal medical treatment as recommended by international guidelines [16]. The decision regarding pre- and post-dilation, and the type and number of stents needed to cover all of the diseased segment will be left to operator’s discretion. Thereafter, FFR or FD-OCT will be performed and further optimization of PCI procedure will be performed as described below.

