If an FFR value of >0.80 is measured on the target AICL, patients will be treated with optimal medical therapy only. If an FFR of ≤0.80 is obtained, patients will undergo a FFR-guided PCI. This means that the patient will undergo conventional PCI with stenting of the AICL in order to achieve a post-stenting FFR ≥0.90. If post-stenting FFR is <0.90 a further post-dilation of the stent will be performed, and if FFR remains at <0.90, a pull-back of the wire to identify another possible pressure drop and/or a subsequent stent implantation at least 5 mm from the stent will be performed according to physician’s preference.

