### Sample size calculation for peri-procedural management costs

The costs for each arm are anticipated to be the combination of diagnostic procedural costs, interventional procedures (eventually derived from the diagnostic ones) and costs related to events occurring during the follow up. On the basis of the NASCI study, we expect a 30% of PCI in the FFR-guided arm [17]. Contrastingly, according to our experience (three years FD-OCT experience at our institution, unpublished data), PCI is anticipated to be performed in about 50% of the FD-OCT-guided arm. Thus considering the mean costs of a FFR-guided PCI (3600€ for PCI + 940€ for the pressure wire + 170€ for adenosine = 4710€) and of an FD-OCT guided PCI (3600€ for PCI + 1600€ for the FD-OCT catheter = 5200€) and the costs of a coronary angiography with FFR (500€ for coronary angiography + 940€ for the pressure wire plus 170€ for adenosine = 1610€) and of a coronary angiography with FD-OCT (500€ for coronary angiography + 1600€ for FD-OCT catheter = 2100€) we expect an overall costs reduction of 30% in the FFR-guidance group compared to the FD-OCT guidance group. Assuming no occurrence, or at least a similar occurrence of MACE, or recurrence of angina at 30 days follow up in both arms, we expect an overall 30% reduction of costs at 30 days follow up in the FFR-guided arm. A total number of 220 patients (110 randomized to FFR guidance and 110 to FD-OCT guidance) with an alpha error of 5% and a beta error of 20% has been calculated to be needed to test this hypothesis.

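### Read literally, the TVR definition omits a first later revascularization of a deferred lesion, and the planned PCI rates make that omission unequal between arms

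*Protocol article*

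**What the plan says.** Under Study endpoints, MACE is "defined as the occurrence of death, myocardial infarction (MI) and target vessel revascularization (TVR), will be prospectively assessed". TVR is its only revascularization component. The first secondary endpoint combines significant angina with MACE at 13 months. If the arms differ in MACE by more than 1 percentage point, that composite becomes the primary endpoint.

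Under Data set and clinical outcome measures, "TVR will be defined as repeated clinically-driven revascularization by either PCI or coronary-aortic bypass grafting involving the treated vessel".

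Many patients will have no index PCI. In the FFR arm, "If an FFR value of >0.80 is measured on the target AICL, patients will be treated with optimal medical therapy only". For both arms, when the criteria are not met, Procedure description says "otherwise the patient will be discharged on optimal medical treatment as recommended by international guidelines". The section on peri-procedural management costs gives the planned shares: "we expect a 30% of PCI in the FFR-guided arm", and "PCI is anticipated to be performed in about 50% of the FD-OCT-guided arm".

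Under FD-OCT guidance, the article cites a 3.2% revascularization rate in the FFR >0.80 group of an earlier trial. It presents this as an adverse event in FFR-negative lesions and as part of the reason for the ulceration criterion.

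**The concern.** The randomized intervention is a rule for treating or deferring a lesion. One plain way for a deferral to fail is that the lesion later needs revascularization, and the article's own rationale treats this as an adverse event. Two words in the TVR definition, *repeated* and *treated*, put it outside the endpoint.

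The arms are planned to defer different shares of patients, so the omission need not cancel. MACE and the composite would then reflect partly how often each arm stented at index and not only how its patients fared. The switch rule adds to this: a shift in the MACE difference can change which endpoint is primary.

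**Working it through.** **1. The plan's own figure.** The composite, which contains TVR, is planned at 25% against 12.5% (mean 18.75%), with alpha 5% and power 80%. With a two-sided test and pooled variance:

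n per arm = [1.96 × √(2 × 0.1875 × 0.8125) + 0.8416 × √(0.25 × 0.75 + 0.125 × 0.875)]² / 0.125² = 2.373 / 0.015625 = 151.9, so 152 per arm and 304 in total.

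This matches the stated 304. The primary endpoint, 20% against 10%, gives 199 per arm (398) against the stated 400.

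**2. Deferred shares.** These are complements of the planned PCI rates; the article does not state them.

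- FFR: 1 − 0.30 = 0.70, or 140 of 200 patients.
- FD-OCT: 1 − 0.50 = 0.50, or 100 of 200 patients.

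**3. Uncounted events.** Let r be the proportion of deferred patients with a clinically driven revascularization of the deferred lesion by 13 months, taken as equal in both arms. Uncounted events are 0.70r and 0.50r, and the gap is 0.20r.

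| r | FFR | FD-OCT | Gap (points) |
|---|---|---|---|
| 1% (assumed) | 0.70% | 0.50% | 0.20 |
| 3.2% (figure in the article) | 2.24% | 1.60% | 0.64 |
| 5% (assumed) | 3.50% | 2.50% | 1.00 |

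At r = 3.2% this is about 4.5 against 3.2 patients per 200. The omission removes more events from the FFR arm and so favours it.

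**4. Where the direction turns.** Setting 0.70 × r(FFR) = 0.50 × r(FD-OCT) gives r(FD-OCT) / r(FFR) = 0.70 / 0.50 = 1.4. Above that ratio the omission favours FD-OCT.

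**5. Link to the switch rule.** 0.20r = 1 point at r = 5%. The same appears from the counted side. Suppose, as an assumption, that 5% of treated and 5% of deferred patients are revascularized later.

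- All later revascularizations: 0.30 × 5% + 0.70 × 5% = 5.0% (FFR) and 0.50 × 5% + 0.50 × 5% = 5.0% (FD-OCT).
- Counted as TVR: 0.30 × 5% = 1.5% (FFR) and 0.50 × 5% = 2.5% (FD-OCT).

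Equal true rates become a counted difference of 1.0 point. The rule acts above 1 point, so this sits on the threshold.

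**6. Effect of counting them on composite power.** Adding 2.24 and 1.60 points without overlap moves the composite from 25% against 12.5% to 27.24% against 14.10%. With 200 per arm, power goes from 0.896 to 0.904, so the fix does not threaten the sample size.

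**The case against.** **The wording may be loose, not exclusionary.** The endpoint is named target vessel revascularization, and the FFR section speaks of a target lesion before any PCI. The follow-up rule in the same section as the TVR definition says "repeat revascularization will be undertaken in the case of significant (>50%) angiographic stenosis", where *repeat* may or may not cover deferred lesions. The sponsor may have meant the vessel of the assessed lesion. This is fair, but the written definition says otherwise and nothing else in MACE catches these procedures. Ambiguity is itself a reason to reword.

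**A reader might infer that failed deferrals are never counted.** That goes too far. An MI or death counts in MACE, and angina persisting at month 13 counts through the questionnaire. If another lesion in the same vessel was stented at index, or a critical stenosis there had already been treated, the vessel could be read as treated.

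**A reader might infer that such procedures must be frequent**, because an eligible lesion is "a coronary lesion with a visually estimated percentage diameter stenosis ranging from between 30 and 80" per cent and can exceed 50% unchanged. The article allows follow-up angiography only for typical symptoms or signs of ischemia on noninvasive testing, so stenosis alone triggers nothing and no frequency follows. The 23% against 5% in the 13-month study in Table 1 is MACE, not revascularization alone. The only usable rate is 3.2%.

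**A reader might infer a loss of power for the primary endpoint**, since PCI during follow-up can relieve angina before month 13. The 20% planning rate is already angina present at follow-up, so taking off a further share for such procedures risks double counting, and the article gives no such share. The TVR wording does not enter the questionnaire endpoint.

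**Equal r is not assured.** The article reports broadly poor accuracy of FD-OCT for an FFR of 0.80 or below, so patients deferred by the two rules may differ. This stands, and the direction is therefore conditional.

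**The size is modest.** At 5% MACE and 200 per arm, the standard error of the difference is √(2 × 0.05 × 0.95 / 200) = 2.2 points. Chance alone will often carry the observed difference past 1 point. The wording adds a systematic shift to that and is not the main driver.

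**Conclusion.** The point holds for MACE and the first secondary composite, and through the switch rule it can bear on which endpoint is primary. As written, a first clinically driven revascularization of a lesion deferred at index is not a TVR event.

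The expected shift is 0.64 points favouring FFR at the article's 3.2%, and 1.0 point at an assumed 5%. It rests on three assumptions: the planned 30% and 50% PCI rates are realised; the 3.2% from an earlier trial's FFR >0.80 group applies to deferred patients in both arms over 13 months; and r is similar between arms, or at least the FD-OCT-deferred rate stays below 1.4 times the FFR-deferred rate.

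The documents do not support a claim that the primary angina endpoint loses power, nor one of a large bias. This is a moderate defect in an endpoint definition and should be corrected before outcomes are analysed.

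**What to change.** Define TVR as any unplanned, clinically driven PCI or bypass, after the index strategy decision, of a vessel containing an assessed study lesion, whether that lesion was treated or deferred at index. Exclude staged PCI that completes the index decision, since Procedure description allows it as a second procedure.

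Use the same wording for the repeated-PCI items under Costs analysis, so that later procedures in deferred patients are costed as well. State whether the assumed 5% MACE rate already includes such procedures, and restate it if not. At r = 3.2% it would become at most 5% + 2.24% = 7.24% in the FFR arm.

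The cost is a change of endpoint wording and a slightly higher counted MACE rate. Record review is planned only for suspected adverse events, so a later procedure in a deferred patient should be listed as a trigger for review and asked about at the 1-, 6- and 13-month contacts. Patient management does not change.

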**Figure 1 F1:**
[figure not shown]
**Study flow chart.** (AS%, percentage of area stenosis; FFR, flow fractional reserve; MLA, minimal lumen area; OCT, optical coherence tomography; PCI, percutaneous coronary intervention; SAQ, Seattle angina questionnaire).

The specific inclusion and exclusion criteria for the study are reported in Table 2.

**Table 2 T2:** Inclusion and exclusion criteria

**Inclusion criteria**	**Exclusion criteria**
**Clinical**	**Clinical**
Age >18 years	Age <18 years
Diagnosis of ischemic heart disease	Inability to give informed consent
	Female with child-bearing potential
**Angiographic**	Life expectancy <12 months
Single vessel disease with angiographically intermediate coronary lesion OR	Factors making clinical follow up difficult (such as no fixed address)
Multivessel disease with only angiographically intermediate coronary lesion OR	Poor cardiac function as defined by left ventricular global ejection fraction ≤30%
Multivessel disease with at least one angiographically intermediate coronary lesion and already treated angiographically critical stenosis	Recent (<7 days) ST-segment elevation Myocardial infarction
	Recent (<48 hours) Non ST-segment elevation myocardial infarction
	Prior ST-segment elevation myocardial Infarction in the territory supplied by the vessel with the intermediate under investigation
	Severe myocardial hypertrophy (interventricular septum thickness >15 mm, ECG Sokolow’s criteria fulfilled)
	Severe valvular heart disease
	Significant platelet count alteration (<100,000 cells/mm3 or >700,000 cells/mm^3^)
	Gastrointestinal bleeding requiring surgery or blood transfusions within the four weeks previous
	History of clotting pathology
	Known hypersensitivity to aspirin, heparin, or contrast dye
	Advanced renal failure with a glomerular filtration rate <30 ml/min

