### Costs analysis

The costs of the procedures will be calculated by determining the amount of guiding catheters, regular wires, pressure wires, FD-OCT-catheters, balloon dilatation catheters, stents, antiplatelet therapy, adenosine, contrast media, and hospital days used for each patient’s procedure. These will be multiplied by the cost of each resource in Euros. Personnel and laboratory time costs will not be included because assumed to be similar between the two strategies.

Costs of repeated PCI without myocardial infarction, repeated PCI in the setting of a non peri-procedural myocardial infarction and coronary artery bypass grafting will be based on the Italian National Health System’s reimbursement rate per diagnosis-related group.

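### Read literally, the TVR definition leaves a first late revascularization of a deferred lesion's vessel out of MACE, the >1% switch rule and the angina-or-MACE composite

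*Protocol article*

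**What the plan says.** The Study endpoints section of the protocol article builds MACE from death, MI and TVR and has no other revascularization component. TVR is defined once, under Data set and clinical outcome measures: "TVR will be defined as repeated clinically-driven revascularization by either PCI or coronary-aortic bypass grafting involving the treated vessel".

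MACE is used in two further places, both under Study endpoints. The first secondary endpoint is significant angina or MACE at 13 months. That composite becomes the primary endpoint "in the case of a MACE rate absolute difference of >1% between the two study arms".

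Both strategies can end in deferral. Procedure description allows PCI only if the arm's criteria are met and otherwise discharges the patient on medical treatment. FFR guidance repeats this: "If an FFR value of >0.80 is measured on the target AICL, patients will be treated with optimal medical therapy only".

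Under FD-OCT guidance, the case for the plaque-ulceration criterion lists the "revascularization rate of 3.2% in FFR >0.80 group of the FAME study" among adverse events that occur in FFR-negative lesions.

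**The concern.** The trial compares two rules for deciding which intermediate lesions to stent and which to leave. The characteristic failure of leaving a lesion is that its vessel later needs PCI or bypass. The TVR sentence carries two conditions, that the procedure be a repeat and that the vessel be a treated one. A first procedure on a deferred vessel meets neither.

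Such events are foreseeable. Study design admits lesions of 30 to 80% diameter stenosis. Follow-up angiography needs symptoms or signs of ischaemia, and then "repeat revascularization will be undertaken in the case of significant (>50%) angiographic stenosis". Many deferred lesions could therefore already meet the stenosis condition at enrolment.

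Consider a deferred patient who returns with angina, has PCI and is free of angina at 13 months. Read literally, that patient is event-free on the composite. A stented patient with the same course counts as an event. The two strategies are expected to defer different shares of patients, so the number of uncounted events may differ by arm.

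**Working it through.** **The plan's own figure.** For the composite (25% vs 12.5%, 5% two-sided alpha, 80% power, pooled variance, no continuity correction), n per arm = [1.960 × √(2 × 0.1875 × 0.8125) + 0.842 × √(0.25 × 0.75 + 0.125 × 0.875)]² / 0.125² ≈ 152. The total of 304 matches the protocol. The same formula for 20% vs 10% gives 199 per arm, 398 in total, against the stated 400. Neither figure is in dispute.

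**Inputs.**
- 200 patients per arm (Sample size calculation for clinical outcome).
- PCI in 30% of FFR and about 50% of FD-OCT patients (Sample size calculation for peri-procedural management costs).
- Late revascularization of 3.2% in FFR-negative lesions (FD-OCT guidance). No time horizon or unit is given, so its use per patient at 13 months in both arms is an assumption.
- 5% MACE in the FFR arm and no MACE difference expected (Sample size calculation for clinical outcome).

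**Patients who depend on the reading.**
- Deferred: 0.70 × 200 = 140 FFR; 0.50 × 200 = 100 FD-OCT.
- At 3.2%: 140 × 0.032 = 4.48 (2.24% of the arm) and 100 × 0.032 = 3.20 (1.60%).
- Gap: 2.24 − 1.60 = 0.64 points. Together 7.7 patients, against 5% × 400 = 20 expected MACE.
- At a common 5%: 3.5% vs 2.5%, gap 1.0 point. At 8%: 5.6% vs 4.0%, gap 1.6 points.

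The counts are approximate. Table 2 admits patients with "at least one angiographically intermediate coronary lesion and already treated angiographically critical stenosis", and a late procedure in a vessel treated for such a stenosis could be TVR even on the literal reading.

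**Direction.** Hold FFR at 3.2% (2.24% of the arm) and vary the rate in FD-OCT-deferred patients:

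| FD-OCT-deferred rate | FD-OCT share of arm | Gap, FFR minus FD-OCT |
|---|---|---|
| 1.6% | 0.80% | +1.44 points |
| 4.48% | 2.24% | 0 |
| 6.4% | 3.20% | −0.96 points |

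**The switch.** With 200 per arm, a difference above 1% means more than 2 patients. The probabilities are exact binomial.
- 5% taken as total MACE, as the protocol presents it. Inclusive reading, 5% vs 5%: 56.4%. Literal reading, 5 − 2.24 = 2.76% vs 5 − 1.60 = 3.40%: 49.4%.
- 5% taken instead as MACE other than these events. Literal: 56.4%. Inclusive: 62.8%. With equal 60%/60% deferral the inclusive figure is 61.9%, so unequal deferral adds about 1 point.

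On either baseline the reading moves the chance of switching by 6 to 7 points.

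**Composite power at 200 per arm.** With every event counted, 25% vs 12.5% gives 89.6%. If every late-PCI patient is angina-free and uncounted, 25 − 2.24 = 22.76% vs 12.5 − 1.60 = 10.90% gives 89.0%.

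**The case against.** The best defence is that the sentence is stock stent-trial wording, carried over loosely, and that inclusion was meant. The endpoint's name refers to the target vessel, and FFR guidance calls a deferred lesion the target lesion. The same sentence describes deferred patients as treated with medical therapy, so that verb is not reserved for PCI. The follow-up rule speaks of repeat revascularization without limiting it to stented patients. Costs analysis prices follow-up PCI only as "Costs of repeated PCI without myocardial infarction"; read strictly, late PCI in most FFR patients would have no cost source, which is implausible.

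This makes inclusion a plausible intention, and a reader should not infer that the authors chose to exclude these events. It does not override the explicit definition. Table 2 uses the same verb to mean revascularized, and no sentence resolves the conflict.

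The second defence is that little depends on it. The composite still captures a late-PCI patient who dies, has an MI or has significant angina at 13 months. The power loss is 0.6 points even if none of them is captured. This stands.

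A reader might also infer that the definition decides which endpoint becomes primary, because in simulation the two readings lead to different switch decisions in about 32% of trials at 3.2%. That is not supported. The figure is about 30% with equal deferral, so it mainly reflects how easily a >1% rule is tripped at this sample size.

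**Conclusion.** The point holds as a defect of definition. Followed as written, the protocol leaves a first clinically driven revascularization of a deferred vessel out of MACE, the switch rule and the composite, although it elsewhere treats such revascularization as an adverse event. At an assumed 3.2% in both arms, about 4.5 FFR and 3.2 FD-OCT patients are affected. The switch then fires in about 49% of trials on the literal reading and 56% on the inclusive one, with 5% as total MACE.

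Two stronger conclusions are tempting and unsupported. The first is that the omission favours FFR because that arm defers more. The 3.2% belongs to FFR-negative lesions, and the protocol notes that "broadly poor accuracy of FD-OCT in detecting a FFR of ≤0.80 has been described", so FD-OCT-deferred lesions may have a different rate. A rate of 4.48% removes the gap and a higher one reverses it. The second is that the primary analysis is compromised. The SAQ endpoint does not use TVR unless the switch fires, and composite power is 89.0% against 89.6%.

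This should be corrected, but it does not threaten the trial. The size rests on the protocol's PCI forecasts and on a revascularization rate quoted without horizon or unit.

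**What to change.** Replace the TVR sentence with: *TVR is any unplanned, clinically driven PCI or coronary bypass grafting, after the index procedure, involving a vessel containing a study AICL, whether or not that lesion was stented at baseline; a staged PCI decided at the index assessment is not TVR.*

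The staged-PCI clause is needed because Procedure description permits a second, planned procedure. Tying TVR to the study lesion's vessel also keeps out vessels stented earlier for unrelated disease, which say nothing about the randomized strategy. The SAQ primary endpoint stays as it is.

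Apply the sentence to all patients, including those already enrolled. Recruitment began in April 2013, so adopt it without sight of events by arm and before the interim analysis of the first 150 patients. Choosing a reading later could be a data-dependent choice.

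No new data are needed, because records of suspected events are already reviewed for MACE. The downside is that MACE and the composite depend somewhat more on revascularization decisions by unblinded physicians, which Study limitations acknowledges. The requirement for symptoms or ischaemia before follow-up angiography limits this but does not remove it.
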